##### Mother and baby affairs (MBA) workshops:

This arm of intervention will involve antenatal workshop and counselling for parents. This will include organizing a lunch for the participant and her family (husband and kids if any). Generally, this is called as “Seemantha” in Kannada similar to “Godhbharai” in northern India and baby shower in other parts of the world. However, the intervention will involve particular components. Such asA brief talk by health professionals on importance of GDM screening and management and other antenatal and postnatal topics.A health-related quiz competition followed by gifts distribution to winners andRole-plays on personal hygiene, the importance of having nutritional food, delivering at the hospital, precautions at the time of delivery, caring for the baby, feeding of colostrum, homemade baby food, immunization, and family planning measures.

Conducted ahead of OGTT, this activity will be done every month in batches for around 25 participants. We will also ensure father’s participation in the program for increased engagement in managing the health of mother and child. Anganwadi Worker (AWW) and Accredited Social Health Activist (ASHA) workers will also be involved.

### Implementation

The research staff will inform the study participants of MAASTHI birth cohort regarding the interventional trial. Upon voluntary informed consent, the research staff will screen the participants for eligibility and will randomly allocate to one of the study arms. Necessary demographic details, socioeconomic status, diet, physical activity are recorded. Participants will be randomly allocated to the study arms-, IVRS arm, MBA arm or control arm. They are invited to undergo the OGTT between 24 to 36 weeks of gestation. A portion of the blood sample will be stored at − 80 degrees for future biochemical and genetic tests.

In addition to the standard care, the MBA arm will receive intervention in the form of awareness workshop from specialist doctors. There will be role plays and quizzes, participants who win will receive small gifts from the study team.

Along with standard care, the IVRS intervention involves calls to pregnant women at specified periodic time intervals providing them with antenatal care tips, and reminder calls for OGTT and follow-up visits to the hospital. They are also given the opportunity to identify any issues or concerns that they may have with IVRS. Through IVRS, participants will be informed that the IVRS supplements, but do not replace, existing clinical services and that all emergencies should be handled by usual means. If the respondent does not wish to continue in the IVRS arm, they will have the option to move out of this arm and continue in the control arm.

The participants in the control group receive standard care; they will be explained the importance of glucose testing in pregnancy and regular follow-ups as scheduled in the study (Table 1). Baseline sociodemographic information will be collected from participants who discontinue.

**Table 1 Tab1:** Interventions for the pregnant mothers and its target behavioral correlates

Content of intervention	Operationalized as	Target Behavioral correlate
Mother and Baby Workshop(MBA)	Workshops on healthy diet, GDM, immunization, seminars, token of appreciation and a meal for the parents	Participants turning up for OGTT,follow up at delivery and 3.5 months
Interactive voice response system (IVRS)	IVRS calls to participants for reminding OGTT, follow up visit, child immunization. Regular IVRS call providing health advice to pregnant women and mothers on diet and child care	Participants turning up for OGTT, follow up at delivery and 3.5 months
Control arm	Providing routine care; study information sheet and the research assistant will provide the date of next visit for follow-up	Participants turning up for OGTT, follow up at delivery and 3.5 months

### Outcome measures

#### The primary outcome is the proportion of participants visiting the hospital for OGTT before 36 weeks of gestation

OGTT requires overnight fasting of minimum 8–12 h; the pregnant women will have to come early morning to the research hospital after which the fasting venous sample will be drawn. The research staff will administer 82.5 g of glucose (equivalent to 75 g of anhydrous glucose) mixed with 250 ml of water. Blood will be drawn again after 2 h, and the blood sugar level is measured. Successful follow-up assessment means that the pregnant woman has completed OGTT before the end of 36 gestational weeks. The response rate is the number of women completing the OGTT divided by the total number of women who were due for undergoing OGTT within  36 weeks of gestation. The loss to follow up is defined as the number of women who missed OGTT divided by the total number of women who completed 36 weeks of gestation. The eligibe duration for undergoing OGTT is 14 weeks, starting from 22 weeks till the end of 36 gestational weeks.

#### Secondary outcome measure

**The proportion of women who complete the follow-up visits at the time of delivery.** Those who complete the follow-up assessment within 1 week of delivery. Successful follow-up assessment is when the follow-up questionnaire and anthropometry within the designated time of 1 week from the date of delivery is complete. Follow-up rate is defined as the numbers of follow-ups done by research staff divided by the total number of eligible live births in the corresponding period in the study population. The loss to follow up rate will be measured as the number of missed follow-ups divided by the total number of eligible live births due in the corresponding period in the study population. The eligible duration of follow-up for this measure is around 18 weeks, calculated from the time of undergoing OGTT to 40 gestational weeks or at the time of delivery.**The proportion of women who complete the 3.5 months follow up visit:** Successful follow-up assessment is defined as completion of follow-up questionnaire and anthropometry of mother and child within 3.5 months since the date of birth. Follow-up rate will be estimated as the number of follows ups done by research staff divided by the total number of 3.5-month-old infants eligible for follow-up during the corresponding study period in the study population. The loss to follow up rate will be measured as the number of missed follow-ups divided by the total number of 3.5-months-old infants during the corresponding study period in the study population. The time frame for the denominator is 32 weeks, calculated from the 22 weeks of gestation till the infant is 3.5 months old.

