##### Interactive voice response (IVR):

IVRS are a type of computer-linked telephone intervention system that could be used to remind the participants about their medicine, treatment or follow up visit. IVR can provide individualized messages to participants and obtain feedback from participants’ responses through voice recognition or touch-tone keypad. IVR systems have shown potential for use as a tool in health care. For example, IVRS as a reminder system helped to increase preventive screening and vaccinations [22], as a means for screening high-risk pregnant women for depression [23]. IVR allows the pregnant women, their family members to interact with a computer system using a telephone. IVR systems are ubiquitous and are used for banking, flight schedules, and product ordering. Socioeconomically disadvantaged populations react favourably to and use IVR systems for extended durations [24]. Studies show that those with a lower income similar to that of our population are more likely to use IVR [25]. Through IVR, women receive a 2–3 min call that informs them about OGTT test dates, to collect their lab test reports, to know where they plan to deliver and reminds them of their follow-up visits. The IVRS will also provide health information on Gestational Diabetes Mellitus (GDM), breastfeeding and immunization. Research suggests that some socially disadvantaged populations are more likely than their advantaged counterparts to text daily [26]. Telephone technologies have an extensive reach, as mobile phone penetration is very high in the target population. In our study population, 58.6% of the women own cell phone, and everyone has at least one cell phone in their family. If the respondent does not wish to continue in the IVRS arm, they will have option to move out of this arm and continue in the control arm.

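### The delivery and 3.5-month follow-up rates are divided by live births and infants rather than by the women randomised to each arm, so women lost early can leave the denominator; the two OGTT rates are also not complements.

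*Protocol article*

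**What the plan says.** All places are in the Protocol article, under Outcome measures unless stated.

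- **OGTT, heading.** "The primary outcome is the proportion of participants visiting the hospital for OGTT before 36 weeks of gestation". No restriction on the participants is given here.
- **OGTT, response.** "The response rate is the number of women completing the OGTT divided by the total number of women who were due for undergoing OGTT". The cut-off is week 36.
- **OGTT, loss.** This is "the number of women who missed OGTT divided by the total number of women who completed 36 weeks of gestation".
- **Delivery, follow-up.** Visits done are "divided by the total number of eligible live births in the corresponding period in the study population".
- **Delivery, loss.** This is "the number of missed follow-ups divided by the total number of eligible live births due in the corresponding period in the study population".
- **3.5 months, follow-up.** Visits done are "divided by the total number of 3.5-month-old infants eligible for follow-up during the corresponding study period in the study population". The matching loss rate uses 3.5-month-old infants without the condition that they be eligible.

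Both secondary outcomes are titled as proportions of women, but the rates beneath the titles count births or infants. The Study population section describes that population as the pregnant mothers of the ongoing cohort, not as a randomised arm. The Statistical analysis section compares the proportion of participants retained in each intervention group with control by a chi-square test, and does not say which set forms the denominator.

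**The concern.** Women enter at 14 to 36 weeks of gestation, so a live birth and an infant reaching 3.5 months come after randomisation. A birth can be counted only if the team learns of it. A woman who drops out of contact during pregnancy is a failure of retention, yet if her delivery is never learned of she adds nothing to the numerator or to the denominator. The rate then describes women who stayed in contact long enough to be counted, not the women randomised.

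The article gives a reason to think that contact differs by arm. The Background says that after the OGTT the team has no further opportunity to meet the women until delivery. IVRS calls fill that gap, and one of their purposes is "to know where they plan to deliver". Control women are asked to see the team when they attend the hospital, so what is known of a control woman's delivery depends more on her attending. An arm in which more births are found gets a larger denominator and can look worse; an arm that loses more women can look better.

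For the OGTT the issue is narrower. Response and loss are presented as counterparts but are taken over different sets of women.

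**Working it through.** **1. The article's own time windows.** The OGTT window runs from 22 to 36 weeks: 36 − 22 = 14 weeks, as stated. The delivery window is given as around 18 weeks: 40 − 22 = 18. The 3.5-month window is given as 32 weeks from 22 weeks of gestation: 18 + 14 = 32. All three reproduce, with 22 weeks as the common start.

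**2. Delivery rate when there is no true effect.** Let *s* be the share of randomised women seen at delivery and *u* the share whose birth the team never learns of. The rate as defined is *s* / (1 − *u*); over all randomised women it is *s*.

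Inputs: *s* = 50% is the Sample size section's assumption for delivery. *s* = 80% matches the Background's report that nearly 20% did not attend at birth. There are 265 women per arm. The values of *u* are **assumptions**; the article gives none.

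| *s*, both arms | *u* control | *u* IVRS | Control rate | IVRS rate | IVRS − control |
|---|---|---|---|---|---|
| 50% | 25% | 10% | 0.50/0.75 = 66.7% | 0.50/0.90 = 55.6% | −11.1 points |
| 50% | 15% | 5% | 0.50/0.85 = 58.8% | 0.50/0.95 = 52.6% | −6.2 points |
| 80% | 15% | 5% | 0.80/0.85 = 94.1% | 0.80/0.95 = 84.2% | −9.9 points |
| 50% | 5% | 5% | 52.6% | 52.6% | 0 |

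In whole women, with the uncorrected chi-square test:

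- Row 1: 133/199 v 133/239, p = 0.017.
- Row 2: 133/225 = 59.1% v 133/252 = 52.8%, a gap of 6.3 points, p = 0.16.
- Row 3: 212/225 v 212/252, p = 0.0005.

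Over all randomised women, both arms give 133/265 = 50.2% in rows 1 and 2, and 212/265 = 80.0% in row 3, with no difference. The sign of the bias follows whichever arm has the larger *u*.

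**3. The two OGTT rates.** Take 265 women in one arm, all due, of whom 204 are tested: response = 204/265 = 77.0%, the current rate in the Sample size section. Suppose, as an assumption, that some untested women do not complete 36 weeks of gestation.

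- None: loss = 61/265 = 23.0%; sum 100%.
- 5% (13 women): loss = (252 − 204)/252 = 48/252 = 19.0%; sum 96.0%.
- 10% (26 women): loss = (239 − 204)/239 = 35/239 = 14.6%; sum 91.6%.

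Response does not move; only the loss rate does. A woman tested at 28 weeks who delivers at 34 is likewise in the first set and not in the second.

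**The case against.** **A live-birth denominator is defensible.** The visits include anthropometry, of mother and child at 3.5 months, and no visit is possible after a stillbirth or infant death. This stands as a reason for a supportive analysis. It does not justify dropping women whose outcome is simply unknown, and the article does not offer it as its reason.

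**The ascertainment bias is inferred.** This also stands. Asking where a woman plans to deliver is not a record of a birth, control women have contact at routine visits, and no comparable route is described for the workshop arm. The delivery loss rate speaks of births due, which could mean expected births and would keep non-attenders in. But the follow-up rate does not use that word, and the article states no way of finding births that is the same in every arm.

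**Two stronger readings are not supported.**

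- A reader might infer that the delivery outcome is restricted to women who had an OGTT, because its period is "calculated from the time of undergoing OGTT to 40 gestational weeks or at the time of delivery". The phrase only sets a time window: the stated 18 weeks is 22 to 40 weeks of gestation. Nothing there makes OGTT completion an entry condition.
- A reader might infer that the tested OGTT response rate is biased too. Being due follows mainly from gestational age, which is known at entry and which calls or workshops cannot change. Completing 36 weeks is a pregnancy status, so a woman who merely leaves the study may still complete them. The loss rate is not named as a tested quantity.

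**The analysis set may be fixed elsewhere.** A fuller document could do so, but this article writes out its numerators and denominators, so the point rests on what it states.

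**Conclusion.** The point holds for the two secondary follow-up outcomes. As defined, their denominators can omit women lost before delivery, and they do not preserve the randomised comparison. The distortion cannot be sized from the article. It depends on the share of births unknown in each arm: about 6 to 11 points under the assumed gaps above, and nil when ascertainment is equal. The larger figures need a wide ascertainment gap together with no effect on attendance, so they illustrate what the rule permits and are not an expected bias.

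For the OGTT, the conclusion is limited to an inconsistency: response and loss are not complements unless the two sets of women coincide.

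**What to change.** 1. For the OGTT, delivery and 3.5-month outcomes, use all women randomised to the arm as the denominator, scoring 1 for a completed visit and 0 otherwise. This also settles that a woman who moves from IVRS to control is counted in IVRS.
2. Define loss to follow-up as one minus the response rate for each outcome.
3. Report, as a sensitivity analysis, the rates after excluding women with a documented event that makes the visit impossible (pregnancy loss, stillbirth, maternal or infant death), applied identically in all arms.

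The wording of the delivery window need not change for this purpose.

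The cost is a rewording of the outcome definitions, with no new data. Reported rates will be somewhat lower, because women with unknown births, and in the main analysis those with pregnancy losses or deaths, count as not completed. The sensitivity analysis shows how much the documented events contribute.

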MAASTHI is a prospective birth cohort with the aim of assessing the effects of glucose levels in pregnancy on the risk of adverse infant outcomes, especially in predicting the possible risk markers of later chronic diseases [18]. The recruitment of the pregnant women in MAASTHI began in April 2016. The current strategy deployed in MAASTHI cohort is to follow up pregnant women for Oral Glucose Tolerance Test (OGTT), at birth and in-person child assessments at 14 weeks, annually during the year 1, 2 and 3 of the child. Currently, we are recruiting around 80 pregnant women per month, with the completion of all their records, anthropometry measurements, and OGTT. Of the eligible pregnant women, only 77% completed OGTT despite offering the test free of cost and repeated reminders by the research team to get tested for gestational diabetes. Once the OGTT is done between 24 and 36 weeks of gestation, there is no further opportunity to meet them again until the delivery. The duration without contact increases the likelihood of attrition. In the intervening period of initial contact and follow-up’s, it is essential that the participants are continuously engaged by the research staff through innovative methods in order to attain better turn up rate for follow up. Despite stringent adherence of including only the residents of the source population, nearly 20% of the women did not attend the follow-up visits at birth. In order to prevent further loss to follow-ups in subsequent visits, we are interested in exploring whether interventions involving Interactive voice response system (IVRS) and conducting mother and baby workshops can improve follow-up rates.

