### Statistical analysis

Descriptive statistics of participants’ baseline characteristics will be presented to assess their comparability. These statistics will be reported as a mean (SD) or median (first quartile, third quartile) for continuous variables, and count (per cent) for categorical variables. Baseline characteristics will include age, education, occupation, income, parity, gestational age, and mobile phone access. We calculate the response rate for OGTT in each of the study arms. For the primary analysis, we will compare the proportion of participants retained during the eligible period in the MBA and IVRS group with those in the control group using a Chi-square test.

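### The delivery follow-up period is dated from the OGTT, so read literally it gives women who miss the test no start date and ties a secondary outcome to the primary one

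*Protocol article*

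**What the plan says.** All references are to the Protocol article.

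- **Delivery period** (Secondary outcome measure): "around 18 weeks, calculated from the time of undergoing OGTT to 40 gestational weeks or at the time of delivery". The follow-up rate is the number of follow-ups done, divided by the eligible live births falling in the corresponding period. The loss-to-follow-up rate uses eligible live births as well.
- **Success at delivery** (same section): "Those who complete the follow-up assessment within 1 week of delivery". The next sentence requires that the questionnaire and "anthropometry within the designated time of 1 week from the date of delivery is complete".
- **3.5-month period** (same section): "The time frame for the denominator is 32 weeks, calculated from the 22 weeks of gestation till the infant is 3.5 months old".
- **OGTT window** (primary outcome): "The eligibe duration for undergoing OGTT is 14 weeks, starting from 22 weeks till the end of 36 gestational weeks".
- **OGTT window** (Implementation): "They are invited to undergo the OGTT between 24 to 36 weeks of gestation". The Background gives the same limits: "Once the OGTT is done between 24 and 36 weeks of gestation, there is no further opportunity to meet them again until the delivery".
- **Expected completion**: the Background and the Sample size section put current OGTT completion at 77%. The Sample size section hopes for a 10-point gain and sets 265 women per arm.

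**The concern.** Completing the OGTT is the primary outcome, and both interventions are designed to raise it. A period that begins at each woman's OGTT exists only for women who had one. If that period decides which live births enter the delivery denominator, the comparison is restricted to OGTT completers. Completers are selected after randomisation and possibly differently in each arm, so randomisation no longer protects the contrast. Any benefit for delivery follow-up that works by bringing more women to the OGTT would also be removed from view.

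The limits raise two further problems. The stated length does not match the stated start, and the 3.5-month outcome in the same section is counted from a different starting point. The stated end, 40 weeks or delivery, comes before most of the week in which a successful assessment may take place.

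**Working it through.** **1. Reproducing the 18 weeks.** The end is 40 weeks (Secondary outcome measure). The OGTT window opens at 22 weeks (primary outcome section).

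40 − 22 = 18. The figure is reproduced exactly, as the time from the opening of the window to 40 weeks.

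**2. The period as worded, from the actual OGTT to 40 weeks.**

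| OGTT at | Weeks to 40 |
|---|---|
| 22 weeks | 40 − 22 = 18 |
| 24 weeks | 40 − 24 = 16 |
| 36 weeks | 40 − 36 = 4 |

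The range is 4 to 18 weeks under the 22-to-36 window and 4 to 16 weeks under the 24-to-36 window. At the window midpoints it is 40 − 29 = 11 and 40 − 30 = 10 weeks. Under the 24-to-36 window, 18 weeks is reached only if the period is allowed to run to a delivery at 42 weeks (42 − 24 = 18; the 42 is an assumption).

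**3. The other secondary outcome.** The 32 weeks is 18 + 14, where 14 weeks is the infant age at the end of observation given in the Abstract. The sum uses the same 22-week origin, and there the text names that origin. The two figures therefore share an origin, but the two descriptions do not.

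**4. Women without a start date.** At 77% completion, 1 − 0.77 = 0.23.

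- Per arm: 265 × 0.23 = 60.95, about 61 women.
- Whole trial: 795 × 0.23 = 182.85, about 183 women.
- In an arm that reaches 87%: 265 × 0.13 = 34.45, about 34 women.

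The number left out would thus differ between arms if the interventions work.

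**5. The end of the period.** Success may occur up to 1 week after delivery. For a birth at 40 weeks, the span from week 22 that includes this week is 41 − 22 = 19 weeks, not 18. An assessment on the day of delivery lies at the limit; one on days 1 to 7 lies beyond it.

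**6. What conditioning on the OGTT could do (illustration only).** Take OGTT completion of 77% v 87%. Assume delivery follow-up of 85% in completers and 30% in non-completers, the same in both arms.

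- All women: 0.77 × 0.85 + 0.23 × 0.30 = 0.7235, and 0.87 × 0.85 + 0.13 × 0.30 = 0.7785. The difference is 5.5 points.
- With 50% in non-completers: 0.7695 v 0.8045. The difference is 3.5 points.
- Completers only: 85% v 85%, difference 0 in both cases.

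The 85%, 30% and 50% are not in the document. The zero follows from assuming equal rates among completers, so this shows the mechanism and does not estimate the bias.

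**The case against.** The strongest reply is that the delivery denominator is written as eligible live births, with no OGTT condition attached, and that the intervention table lists OGTT attendance and delivery follow-up as separate targets in every arm. On this view the reference to the OGTT is a loose way of naming the opening of the OGTT window, as the arithmetic suggests. An analyst who used all live births would do the right thing.

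This stands in part. The document does not state a restriction to completers. But it links the denominator to the corresponding period and dates that period from the OGTT, so the written rule permits the restriction.

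A reader might infer several stronger points that the document does not support:

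- *That 18 weeks is impossible.* It is not: an OGTT at 22 weeks, which the primary outcome section allows, gives exactly 18, and the text says the length is approximate.
- *That every valid delivery assessment is misclassified.* The success definition explicitly allows 1 week, a same-day assessment falls at the limit, and the period may be meant only to fix which births count.
- *That births after 40 weeks are excluded.* The alternative end at delivery can be read as covering them. The text is unclear, not exclusionary.
- *That the Statistical analysis section applies these limits.* Its plan to "compare the proportion of participants retained during the eligible period" stands in the sentence on the primary analysis and most naturally refers to the OGTT window.

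**Conclusion.** The point holds as a defect in the definition of a secondary outcome. The 18 weeks describes a fixed 22-week start, while the words describe each woman's OGTT, from which the time to 40 weeks is 4 to 18 weeks (4 to 16 under the window in the Background and Implementation). Applied literally, about 61 of 265 women per arm at the current completion rate would have no period, and the comparison would depend on a post-randomisation outcome that the interventions target. The stated end does not cover the 1-week assessment window and leaves late births unclear.

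The 61 assumes that 77% completion carries over to the trial. No size can be put on the bias from the document, because follow-up by OGTT status is not given. The primary outcome and the sample-size arithmetic are not affected by this point.

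**What to change.** State that the denominator for the delivery outcome is all eligible live births among all randomised women, in their assigned arm, whether or not they had the OGTT and whatever the gestational age at delivery. State that success is an assessment completed up to 7 days after the actual delivery date. Use one origin that does not depend on the OGTT for both the delivery and the 3.5-month outcomes, and restate the 18-week and 32-week figures from it or delete them. Reconcile the 22-to-36 and 24-to-36-week OGTT windows; which of them is right is for the investigators.

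The cost is small: a change of wording in two outcome definitions, plus obtaining birth status and delivery date for women without an OGTT. A denominator of live births already requires the birth status.
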